# Is an in-home telerehabilitation program for people with proximal humerus fracture as effective as a conventional face-to face rehabilitation program? A study protocol for a noninferiority randomized clinical trial

**DOI:** 10.1186/s13102-016-0051-z

**Published:** 2016-08-26

**Keywords:** Rehabilitation, Proximal humerus fracture, Telerehabilitation, Effectiveness

## Abstract

**Background:**

Proximal humerus fractures can be treated surgically (eg: pinning, plate and screws) or conservatively by wearing a splint or a cast. Following both of these approaches, rehabilitation has proven effective to prevent functional limitations and to re-establish normal shoulder function. However, access to these rehabilitation services and compliance tends to be limited in elderly patients due to travelling difficulties caused by their precarious health status and, in some cases, social and marital status. Since the majority of patients with a proximal humerus fracture are elderly, it becomes relevant to find a new way to offer quick, simple and suitable rehabilitation service. Thus, the use of promising alternative approaches, as in-home telerehabilitation, can enhance access to rehabilitation services for such population. The main objective of the study is to compare the clinical effects of the innovative telerehabilitation approach (TELE group) compared to face-to-face visits to a clinic (CLINIC group) for patients treated for a proximal humerus fracture.

**Methods/Design:**

In this randomized controlled trial, individuals who have had a proximal humerus fracture treated conservatively at the Centre intégré universitaire de santé et de services sociaux de l’Estrie - Centre hospitalier universitaire de Sherbrooke (CIUSSS de l’Estrie CHUS), and who are returning home will be included. Participants will be recruited during their visit to the emergency ward or outpatient clinic by the medical or research team and will then sign the informed consent form if they are interested to participate in the study. We expect to recruit 52 participants (26 per group). Randomization will be done by a random number generator with sealed envelopes. Each patient will be evaluated before the beginning of the rehabilitation (T1), and immediately after the 2-month intervention (T2). The following outcomes will be measured: 1) upper extremity function (Constant Shoulder Score and Disability of the Arm, Shoulder and Hand questionnaire [DASH]); 2) range of motion (conventional goniometer); 3) user satisfaction (Health Care Satisfaction questionnaire); and 4) cost of services to the public healthcare system.

The difference between the two groups will be compared using a *t*-test or a chi-squared test, and through a cost-effectiveness economic analysis.

**Discussion:**

We hypothesize that in-home telerehabilitation will provide a good alternative to conventional rehabilitation, in terms of its efficacy, simplicity, patient satisfaction, and low associated costs.

**Trial registration:**

ClinicalTrials.gov: NCT02425267. April 22^nd^, 2015.

## Background

The aging population has placed in interesting pressure on our health system. In addition to different age-related conditions, the prevention and treatment of fragility fractures has become an important issue. Although osteoporosis treatments have improved in recent years, in addition to falls, the associated fractures are highly related to morbidity and mortality. Each year, one person out of three falls, and from them, 10 % causes a fracture [1]. The proximal humerus is one of the three most common fractured sites, along with the hip and wrist, making up 4 to 5 % of fractures, all sites combined [2].

Humerus fractures can be treated surgically (e.g. pinning, plate and screws, etc), or conservatively, typically through immobilisation in a splint or an orthotic device [3]. Conservative medical treatment tends to be advocated, mostly because of the complications that may occur following surgical intervention. However, the type of fracture, the surgeon, the patient and the fracture classification will influence the treatment decision. Among the existing proximal humerus fracture classifications (i.e. Neer [4], AO [5], Codman-Hertel [6], and Resch [7]), the Neer classification is the most widely used among orthopaedists. Neer group I and II fractures are often treated with the conservative approach, while group III and IV fractures most likely are surgical cases [8, 9]. Following both of these medical approaches, the individual needs rehabilitation to prevent functional limitations. Indeed, intervention programs in rehabilitation for humerus fractures have demonstrated their efficacy to improve shoulder joint mobility, diminish pain and improve functional state [10, 11].

Immobilisation time between the fracture and the beginning of rehabilitation is a parameter that has a significant influence on conservative treatment outcome [10–12], and, in reality, varies greatly between cases. A recent randomised clinical trial (RCT) [12] addressed the question of the efficacy of an immediate versus delayed mobilisation, showing that patients with a shorter immobilisation time (1 week) recovered faster functionally than patients with a longer immobilisation time. A similar study demonstrated that, in addition to a faster functional recovery, an immediate rehabilitation following the fracture leads to experiencing less pain for the patient [11]. Another study even claimed that a 3-day immobilisation, followed by passive mobilisation is sufficient and safe to restore physical capacities and post-fracture performance [10]. Finally, a RCT has compared the difference between the efficacy of a conventional physical therapy treatment and an individual in-home training program with instructions [13]. The results demonstrated no significant difference between treatment types. Interestingly, advantages emerged in the individual approach with instructions, such as: 1) allowing the patient to stay at home while receiving their rehabilitation, eliminating the need to travel to a clinic, and 2) patient satisfaction derived from having the responsibility of their rehabilitation at home.

Presently, in Canada, rehabilitation for proximal humerus fractures occurs at the hospital (37.2 %) [14], in external clinics, and in various in-home services. However, not all patients have access to rehabilitation services, mainly due the difficulty of the elderly to travel to the clinic because of their precarious health condition [15]. Therefore, new service delivery strategies are essential to enhance accessibility to rehabilitation services, with a focus on in-home services. Telerehabilitation, defined as a telehealth application that uses telecommunication technologies to provide physical therapy services [16–19], is an interesting solution to the lack of available services. This approach allows the patient to receive rehabilitation at home, without the need for a health care professional to travel to the patient’s home or to travel to the clinic for the patient. As such, telerehabilitation could permit the elderly with a proximal humerus fracture to have access to rehabilitation directly in their home with adequate and safe supervision. Services provided by telerehabiliation can be very diverse, including telecheckups (phone calls to ensure the wellness of the patient), telemonitoring (record physiological data), teleconsultation (between two service centers) and teletreatment [19, 20]. This long-distance therapeutic intervention also includes the notion of frequency (a set number of sessions per week) and duration (over a specific time period) [21, 22].

A systematic review of telerehabilitation interventions [18] showed a tendency for these services to generate clinical improvements that are generally equal to those resulting from conventional rehabilitation programs. For example, efficacy of teletreatment has been demonstrated: in older populations with loss of autonomy [23], or living at home will mild to moderate dementia [24]; in individuals with mobility impairments [25]; and following total knee [26–29] or shoulder [30] arthroplasty. Interestingly, in the latest study [30], rehabilitation treatment was provided to 10 elderly patients through a videoconferencing system installed directly in their home. The intervention period length was 2 months and included supervised sessions, where a physical therapist was able to adapt exercises according to each patient’s evolution. Results of this study demonstrated that patients are able to adhere to teletreatment, and that they are able to maintain a good relationship with their physical therapists even though there was no direct physical interaction. Moreover, this remote method of receiving their rehabilitation facilitated their daily living since they were not required to travel to receive treatment. By staying home, patient motivation increased and they felt more independent in their exercises. However, an important limitation to this study was the lack of evaluation of clinical results. Therefore, although a promising avenue for rehabilitation, especially in older populations, the efficacy and functional results of telerehabilitation remain to be studied with high quality evaluations.

To our knowledge, only one study exists on telerehabilitation among patients with a proximal humerus fracture [31]. This study, realised by our research team, demonstrated the feasibility of such a service delivery to this specific population. However, our previous study was more focussed on proof-of-principle, and as such, the lack of a control group (treatment at clinic) did not permit us to affirm that clinical improvement was due to the patient’s natural recovery or to the telerehabilitation received. Thus, the main objective of the present study is to evaluate the efficacy of in-home telerehabilitation (TELE group) compared to the conventional rehabilitation in a clinic (CLINIC group) in a population with a proximal humerus fracture. Our hypothesis is that in-home telerehabilitation will prove to be a good alternative to conventional rehabilitation.

## Methods/Design

### Study design

In our study, teletreatment will be used to provide physical therapy sessions from a service center (clinic) directly into the patients’ home. The study design is a RCT. As described in Fig. 1, there will be an evaluation at baseline (T1), 1 to 2 weeks post-fracture. Then, the 8-week intervention phase (telerehabilitation) or conventional rehabilitation in a clinic will begin at the moment prescribed by the orthopaedist, approximately 2 to 3 weeks post-fracture. Finally, a second evaluation (T2) will be held at the end of the intervention period.

**Fig. 1 Fig1:**
[figure not shown]
Study timeline. The patient is recruited post-fracture and evaluated at baseline (T1). Then, the participant is randomized into either Telerehabilitation group or Conventional rehabilitation group. Following 8 weeks of treatments, the patient is evaluated again (T2)

### Participants

This study will be conducted in the population with a proximal humerus fracture treated conservatively at the Centre intégré universitaire de santé et de services sociaux de l’Estrie - Centre hospitalier universitaire de Sherbrooke (CIUSSS de l’Estrie CHUS). To be included, participants will have to: 1) return home after discharge from hospital or emergency; 2) be apt to do exercises; 3) have a sufficient verbal and written comprehension to participate to the treatment and evaluations; 4) have access to high speed internet connection at home. Participants with the following characteristics will be excluded from the study: 1) intra-articular proximal humerus fracture types (often susceptible to longer rehabilitation periods and a higher risk of complications); 2) presence of any other upper-limb fracture that can interfere with rehabilitation; and 3) surgical treatment following the fracture.

A sample of 52 participants with a proximal humerus fracture and responding to the eligibility criteria will be included. Participants will be screened by the orthopaedic research team through the orthopaedic resident or nurse who proceeds to the installation of the removable splint. At that time, the research team will briefly inform the patient on the study and will obtain his/her authorisation to be contacted by phone by a member of the teletreatment research for a more detailed evaluation of eligibility and explanation of the study. Following this telephone interview, if the participant is still interested and meets all the eligibility criteria, an appointment will be scheduled to obtain the informed consent (approved by local ethic committee; CIUSSS de l’Estrie - CHUS, and perform the first evaluation (T1). Immediatly following visit T1, each patient will be randomised to either the TELE or the CLINIC group. The randomised list has been generated electronically using block randomization of size 4. The evaluator is the only one who will be blind to the randomisation.

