### Statistical methods

The principal analyses intend to test the noninferiority of the TELE intervention versus the CLINIC intervention. We aim to recruit a total of 52 participants, or 26 participants per group. Sample size was determined with data from a previous study on the Constant score [44], which is considered in this study as the primary outcome measure. With 26 participants per group, within the context of a unilateral t-test with an alpha level set at 0.05, the power of the study to reject non-equivalence hypothesis would be at 69 % for a difference of 10.3 or less (standard deviation = 17). This noninferiority point is under the minimal clinically important difference of 10.4 points on the Constant score [44].

Participant characteristics in each group will be described pre-intervention (T1) using mean and standard deviation (continuous variables) or proportion (categorical variables). Groups at baseline will then be compared using *t*-test or chi-squared test.

First, the data will be analysed according to the received intervention (per protocol), and then, according to the assigned group (intention to treat analysis). A sensitivity analysis will be used to explore the effect of compliance or screen failures: missing data will be replaced by extreme data (no change following intervention or most favorable change noted in the study). Any non-robustness of the revealed results by comparison of strategies will be noted.

Economic analysis is of cost-efficacy type. Cost by change-unit of the principal dependant variable (Constant score) will be determined for both groups. Differential cost will then be established.

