## Discussion

This trial is the next logical step to the feasibility study conducted by our research team on 12 post-proximal humerus facture patients [31]. The previous study demonstrated that telerehabilitation seems to be a promising avenue to provide rehabilitation services to this population without adverse events. The results obtained following the present protocol will affirm the cost-efficacy of telereahabilitation treatment in an orthopaedic context, more precisely, after a proximal humerus fracture treated conservatively.

In order to control a potential selection bias, randomisation will be blind to the evaluator and participants’ characteristics will be compared pre-intervention between each group. If a group differs on some characteristics despite randomisation, corrective measures will be made in subsequent analyses. Furthermore, information bias will be controlled by using standardized measures and by calibrating all the assessors for each assessment.

This study will verify the noninferiority of in-home telerehabilitation compared to face-to-face intervention at a clinic for patients with proximal humerus fracture. In accordance with our hypothesis, we think that telerehabilitation will improve access to a rapid, less expensive, satisfactory and effective rehabilitation services.

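### The fixed, published block size of 4 could let a well-informed recruiter at this single centre foresee up to one third of assignments, and evaluator blinding does not guard against that

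*Protocol article*

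**What the plan says.** All references are to the protocol article.

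- **List** (Participants): "The randomised list has been generated electronically using block randomization of size 4". No second block size and no stratification factor is mentioned.
- **Size and ratio** (Statistical methods): "We aim to recruit a total of 52 participants, or 26 participants per group".
- **Centre** (Participants): recruitment is from one hospital organisation, so there is one sequence to follow.
- **Blinding** (Participants): "The evaluator is the only one who will be blind to the randomisation". The arms differ visibly in delivery mode, so the trial is in effect open-label.
- **Path to randomisation** (Participants): an orthopaedic resident or nurse screens at the splint fitting. The patient is then "contacted by phone by a member of the teletreatment research for a more detailed evaluation of eligibility and explanation of the study". Consent and T1 follow at a booked appointment. Finally, "Immediatly following visit T1, each patient will be randomised to either the TELE or the CLINIC group".
- **Concealment** (Abstract, Methods/Design): "Randomization will be done by a random number generator with sealed envelopes".
- **Stated protection** (Discussion): "In order to control a potential selection bias, randomisation will be blind to the evaluator". The same sentence goes on to a comparison of the groups at baseline, and the next one promises corrective measures in the analysis if they differ.
- **Dates**: recruitment had been running since June 2015 (Trial status). The article is dated 26 August 2016.

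**The concern.** In a permuted block of fixed, known size, past allocations reveal some future ones. Once one arm has used its two places in a block of 4, the rest of that block is settled. Anyone who knows the size and has followed the sequence can then foresee the next arm before the next patient is invited.

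Two steps before consent leave room for judgement: the screening and the eligibility phone call. Fitness for exercise and sufficient comprehension are both assessed by staff. A patient who seems ill suited to video sessions could be delayed or discouraged when the next place is known to be TELE. The arms could then differ in motivation or ease with technology, which the baseline comparison cannot detect and an adjustment cannot remove unless they are measured.

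The Discussion assigns the wrong safeguard to this threat. A blinded evaluator protects the measurement of the outcome. Who enters next, and into which arm, is protected by concealment and unpredictability of the allocation.

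**Working it through.** The article gives no predictability figure to reproduce. Its one design calculation, 69% power, does reproduce (69.5% by noncentral t, one-sided 0.05, 26 per arm, margin 10.3, SD 17, true difference 0) and is not affected by this point.

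**Inputs.** Block size 4 (Participants); 52 patients, 26 per arm (Statistical methods), so 52/4 = 13 blocks. A 1:1 block of 4 has 4!/(2!·2!) = 6 equally likely orders.

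**Assignments that are certain, with complete knowledge of the past.**
- Positions 1 and 2: probability 0.
- Position 3: certain if the first two match, 2/6 = 1/3.
- Position 4: always certain, 1.
- Per block: 0 + 0 + 1/3 + 1 = 4/3. Share: (4/3)/4 = 1/3.
- Over 13 blocks: 13 × 4/3 = 17.3 of 52. Each block has 2 certain places with probability 1/3 and otherwise 1, so the variance per block is 2/9, the SD is √(13 × 2/9) = 1.7, and the possible range is 13 to 26.

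**Best guess (always name the arm that is behind in the block).**
- Chance of being right at positions 1 to 4: 1/2, 2/3, 1/3 + (2/3)(1/2) = 2/3, and 1.
- Sum 17/6 per block; (17/6)/4 = 70.8%, against 50% by chance. Over the trial: 13 × 17/6 = 36.8 of 52.

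**Effect of pending patients.** The relevant moment is screening or the phone call, which comes before randomisation. Earlier patients may then still be waiting.
- One pending: only position 4 can be certain, and only if positions 1 and 2 match. Share (1/3)/4 = 8.3%, or 4.3 of 52.
- Two pending: at position 4 only position 1 is known, so nothing is certain. Share 0.

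The article gives no recruitment rate, so the share at the pre-consent steps lies between 0 and 33%.

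**Other block designs, for comparison.**

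| Design | Certain share | Of 52 | Best guess right |
|---|---|---|---|
| Fixed 4 | 33.3% | 17.3 | 70.8% |
| Fixed 6 | 25% | 13 | 68.3% |
| Fixed 8 | 20% | 10.4 | 66.6% |
| Random mix 4/6 | about 6% | about 3 | not computed |
| Random mix 4/6/8 | about 2% | about 1 | not computed |

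The fixed designs are by enumeration. The mixed designs are simulated over 52 patients, and an assignment counts as certain only if every block path consistent with the past agrees.

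**The case against.** The strongest reply is that the one-third figure needs three things the article does not establish.

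1. **Knowledge of the sequence.** That only the evaluator is blind means others may know a patient's arm. It does not mean that the resident, the nurse or the caller keeps an ordered record of all allocations. Who takes consent, opens envelopes and holds the list is not stated, and an article may leave that to the full protocol. This stands: access to the past sequence is a condition of the calculation, not a documented fact.
2. **No overlap between patients.** Splint fitting, phone call and T1 appointment are separate steps, with T1 one to two weeks after the fracture. Any overlap lowers predictability quickly. This also stands.
3. **Knowledge of the block size.** Publication cannot have affected allocations before August 2016, and nothing says that recruiters knew the size earlier. This stands for the earlier patients. For any recruited afterwards, the size is public.

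The envelopes and the baseline checks are also real safeguards. Envelopes hide the next card, but they do not prevent deduction from the cards already opened. Baseline comparison and later correction reach only what was measured.

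A reader might infer that one third of assignments were in fact known, or that patients were steered. The documents support neither. A reader might also infer a bias toward similarity that makes noninferiority easier to show. That does not fit the mechanism: steering makes the arms differ, and the article gives no basis for its direction or its size on the Constant score.

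**Conclusion.** The point holds as a risk created by a stated design choice, together with an incorrect statement in the Discussion. Up to one third of assignments (expected 17 of 52) could be foreseen with certainty, and 71% guessed correctly, under three conditions: the recruiter knows the block size, knows every past allocation in order, and has no earlier patient pending. With one pending the certain share is about 8%; with two it is zero. These figures measure predictability, not bias in the treatment effect. The arithmetic is exact; whether the conditions were met is unknown. The correction of the Discussion sentence does not depend on any of them.

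**What to change.** **List.** For patients not yet randomised, replace the remaining envelopes with a new list using randomly varying block sizes. Do not disclose the sizes to recruiting staff, and have existing staff outside recruitment prepare and hold the list. This chiefly removes certainty. Some advantage in guessing remains in any blocked design, as the fixed block of 8 shows.

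**Text.** In the Discussion, tie selection bias to allocation concealment and detection bias to evaluator blinding. Keep the baseline comparison as a check on measured characteristics only.

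**If recruitment is already complete**, the list cannot be changed. Correct the sentence, and report who held the list and who knew the block size.

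**Cost.** A new list, new envelopes and possibly a final imbalance of a few patients. The loss of precision is negligible: a 28:24 split gives √(1/28 + 1/24) = 0.2782 against √(2/26) = 0.2774, a standard error 0.3% larger.

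### As worded, the blinding rule leaves the outcome analyst unmasked while baseline-imbalance corrections remain to be decided from the data; this permits, but does not itself cause, a higher false-noninferiority rate

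*Protocol article*

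**What the plan says.** The Participants section closes its account of screening, consent, baseline assessment and allocation with: "The evaluator is the only one who will be blind to the randomisation". The main Discussion section repeats the point as a bias control: "randomisation will be blind to the evaluator and participants’ characteristics will be compared pre-intervention between each group". Neither place mentions an analyst.

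The next sentence of the Discussion sets a rule that depends on the data: "If a group differs on some characteristics despite randomisation, corrective measures will be made in subsequent analyses". It does not say which characteristics count, what size of difference triggers a correction, or what the correction is.

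Statistical methods makes noninferiority on the Constant score the principal question, "within the context of a unilateral t-test with an alpha level set at 0.05". It runs a per-protocol analysis and then an intention-to-treat analysis, adds a sensitivity analysis with extreme values for missing data, and undertakes to report any lack of robustness across these strategies.

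Patients' satisfaction includes a telemedicine questionnaire given to the TELE group only. Costs describes cost data collected for both delivery modes.

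**The concern.** Patients and therapists cannot be masked to home video versus clinic visits. The analyst can be, and the exclusive wording in Participants rules that out without giving a reason. This is a statement in the text and not a detail left to another document: an analysis plan that masked the analyst would contradict the published sentence.

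It matters here because the Discussion foresees an adjustment decided after the baseline data have been seen. If the person deciding also knows the arms and can see the outcome, the more favourable of several defensible analyses can be preferred, even without intent. In a noninferiority trial the error at stake is declaring TELE noninferior when its true deficit equals the margin.

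**Working it through.** **1. The plan's own figure.** Inputs from Statistical methods: 26 per group, margin 10.3, SD 17, one-sided alpha 0.05.

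- Standard error = 17 × √(2/26) = 4.715.
- Margin / standard error = 10.3 / 4.715 = 2.185.
- Normal approximation: Φ(2.185 − 1.645) = Φ(0.540) = 70.5%.
- Noncentral t with 50 degrees of freedom: 69.5%.

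The plan states that "the power of the study to reject non-equivalence hypothesis would be at 69" per cent, so its figure reproduces. The inputs are therefore a fair base for the simulation.

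**2. Error with a single fixed analysis.** Data were simulated with a true TELE deficit of exactly 10.3, 26 per arm and SD 17, in 20,000 runs per setting. The baseline-T2 correlation is not given in the article, so 0.3, 0.5 and 0.7 were assumed. Three analyses were considered: a t-test on the T2 score, a t-test on change from T1, and a baseline-adjusted comparison. Each alone rejected in about 5% of runs (4.8% to 5.3% across repeats). Knowing the arms does not move this number.

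**3. Error when the most TELE-favourable analysis is picked.**

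| Rule | r = 0.3 | r = 0.5 | r = 0.7 |
|---|---|---|---|
| Pick allowed only if baseline Constant differs at p<0.05, otherwise T2 t-test | 6.0% | 5.8% | 5.3% |
| Same, trigger p<0.10 | 6.6% | 6.3% | 5.6% |
| Pick always allowed | 8.9% | 9.3% | 9.5% |
| Fixed rule: adjust if p<0.05, no picking | 5.0% | 4.6% | 3.9% |

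The first two rows respect the condition in the Discussion, with the p-value triggers as assumptions. The third row ignores that condition and is a worst case; a separate run of it gave 8.6%, 9.0% and 9.4%. The Monte Carlo standard error near 6% is √(0.06 × 0.94 / 20,000) = 0.17 percentage points. A repeat with 100,000 runs, setting the SD at T1 also to 17, gave 5.5% to 6.5% for the conditional rows and 8.8% to 9.6% for the unconditional row.

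**4. A wider set of choices.** A second simulation (4,000 runs per setting) assumed four candidate covariates and 10% or 20% randomly left out of the per-protocol set. The most favourable pick across both analysis sets and all single-covariate adjustments gave 9.5% to 11.8%. Requiring both sets to pass gave 2.8% to 3.6%, but the article does not state that requirement. These figures rest on covariates and exclusion rates that the article does not give, so they are not carried into the verdict.

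**The case against.** The strongest reply is that the sentence sits in a paragraph about recruitment and allocation. Its natural purpose is to say that patients, therapists and coordinators will know the arm. No passage says who analyses the data, or who makes the open choices and when. Covariates, compliance definitions and missing-data rules commonly sit in a full protocol or analysis plan, neither of which is shown. If those are fixed in advance, the error returns to about 5% whether or not the analyst is masked.

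Much of this stands. The missing details are not faults in themselves. The commitment in Statistical methods to run both analysis sets and report non-robustness is a partial guard, though it does not clearly reach the baseline corrections in the Discussion. What remains is that the exclusive wording, taken literally, covers the analyst and would have to change if the analyst were masked.

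Two stronger readings are tempting:

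- A reader might infer that unmasking inflates the error rate. The documents do not support that: inflation also needs choices still open at analysis and made in TELE's favour, and the article establishes neither.
- A reader might infer a motive from the account of the telerehabilitation platform or from the forecast that "we think that telerehabilitation will improve access to a rapid, less expensive, satisfactory and effective rehabilitation services". The platform section reports joint development with a vendor but does not say that the study team, still less the analyst, built it. The forecast is an ordinary study hypothesis.

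**Conclusion.** The point holds as a moderate weakness of wording and safeguard, not as a demonstrated error-rate fault. The literal text leaves the outcome analyst unmasked and leaves imbalance-triggered corrections to be settled from the data. Against a nominal 5%, the exposure is about 5.3% to 6.3% if a favourable pick is confined to trials with a baseline Constant difference at p<0.05 or p<0.10; one of the six settings reached 6.6%. It is about 9% only if the pick is unconstrained. More covariates or a looser trigger would raise the conditional figure. All of these rest on 26 per arm, SD 17, an assumed correlation of 0.3 to 0.7, and a pick that always favours TELE.

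**What to change.** Replace the sentence in Participants with wording to this effect: *Patients and treating therapists will know the allocation; the evaluator and the outcome analyst will not.* Then state that:

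- the analysis file carries arms coded A and B;
- the TELE-only telemedicine questionnaire and the cost data, which would reveal the arm, are held in a separate file;
- the primary analysis choices, including any baseline adjustment and what triggers it, are locked and dated before the code is broken and that file is released.

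The reference to baseline corrections in the Discussion should point to that locked decision.

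The cost is a recoded arm variable and a two-step data release by an existing team member other than the analyst. The article does not describe staffing, so it is an assumption that such a person is available. The total of 52 participants and the stated 69% power are unaffected. Because only the release of data changes, this can be adopted although recruitment has begun.
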